#### 11.1.2 Consent for minors when they reach the age of majority

Not applicable

#### 11.1.3 Considerations for Consent of NIH staff, or family members of study team members

Not applicable

#### 11.1.4 Consent of Subjects who are, or become, decisionally impaired

Adults unable to provide consent are excluded from enrolling in semi-structured interviews.

### 11.2 Study Discontinuation and Closure

This study may be temporarily suspended or prematurely terminated if there is sufficient reasonable cause. Written notification, documenting the reason for study suspension or termination, will be provided by the suspending or terminating party to the investigator, funding agency, and regulatory authorities. If the study is prematurely terminated or suspended, the Principal Investigator (PI) will promptly inform study practices, the Institutional Review Board (IRB), and sponsor/funding agency and will provide the reason(s) for the termination or suspension. Study participants will be contacted, as applicable, and be informed of changes to the study visit schedule.

Circumstances that may warrant termination or suspension include, but are not limited to:

- Determination of unexpected, significant, or unacceptable risk to participants
- Demonstration of efficacy that would warrant stopping
- Insufficient compliance of study staff to the protocol requirements
- Data that are not sufficiently complete and/or evaluable
- Determination that the primary endpoint has been met
- Determination of futility

The study may resume once concerns about safety, protocol compliance, and data quality are addressed, and satisfy the NIA or other relevant regulatory or oversight bodies (OHRP, DSMB).

### 11.3 Confidentiality and Privacy

Participant confidentiality and privacy is strictly held in trust by the participating investigators, their staff, the safety and oversight monitor(s), and the sponsor(s) and funding agency. This confidentiality is extended to the data being collected as part of this study. Data that could be used to identify a specific study participant will be held in strict confidence within the research team. No personally identifiable information from the study will be released to any unauthorized third party without prior written approval of the sponsor/funding agency.

All research activities will be conducted in as private a setting as possible.

***Population cohort data.*** Study participant research data for the population cohort, which is for purposes of statistical analysis and scientific reporting, will be transmitted as limited datasets to UCLA, and will be stored at UCLA. The study data management systems used by the DARTNet Institute, AAFP NRN, and UCLA research staff will be secured and password protected.

***Semi-structured interview data.*** For semi-structured interview participants, contact information will be securely stored on a secure network server at UCLA for internal use during the study or on a UCLA-approved HIPAA-compliant cloud storage solution such as BOX. At the end of the study, all records will continue to be kept in a secure location for as long a period as dictated by the reviewing IRB, Institutional policies, or sponsor/funding agency requirements, after which patient contact information will be deleted. Audio recordings and de-identified transcripts of audio recordings will be maintained indefinitely.

***Survey data.*** Survey data will be securely stored on UCLA Health Qualtrics or REDCap, both of which are HIPAA-compliant survey platforms.

#### 11.3.1 Measures Taken to Ensure Confidentiality of Data Shared per the NIH Data Sharing Policies

It is NIH policy that the results and accomplishments of the activities that it funds should be made available to the public (see <https://grants.nih.gov/policy/sharing.htm>). The PI will ensure all mechanisms used to share data will include proper plans and safeguards for the protection of privacy, confidentiality, and security for data dissemination and reuse (e.g., all data will be thoroughly de-identified and will not be traceable to a specific study participant). Plans for archiving and long-term preservation of the data will be implemented, as appropriate.

#### 11.3.2 Certificate of Confidentiality

To further protect the privacy of study participants, the Secretary, Health and Human Services (HHS), has issued a Certificate of Confidentiality (CoC) to all researchers engaged in biomedical, behavioral, clinical or other human subjects research funded wholly or in part by the federal government.  Recipients of NIH funding for human subjects research are required to protect identifiable research information from forced disclosure per the terms of the NIH Policy (see <https://humansubjects.nih.gov/coc/index>). As set forth in [45 CFR Part 75.303(a)](https://www.ecfr.gov/cgi-bin/text-idx?SID=f3e9328bbbd5aabe8e639ca48dcbcc7f&mc=true&node=se45.1.75_1303&rgn=div8) and [NIHGPS Chapter 8.3](https://grants.nih.gov/grants/policy/nihgps/HTML5/section_8/8.3_management_systems_and_procedures.htm), recipients conducting NIH-supported research covered by this Policy are required to establish and maintain effective internal controls (e.g., policies and procedures) that provide reasonable assurance that the protocol is managed in compliance with Federal statutes, and regulations. It is the NIH policy that investigators and others who have access to research records will not disclose identifying information except when the participant consents or in certain instances when federal, state, or local law or regulation requires disclosure. NIH expects investigators to inform research participants of the protections and the limits to protections provided by a Certificate issued by this Policy.

### 11.4 Future use of Stored Specimens and Data

Data collected for this study will be analyzed and stored at the University of California, Los Angeles. After the study is completed, de-identified, archived data will be transmitted to and stored at Dryad (through the University of California), for use by other researchers including those outside of the study. Permission to transmit data to Dryad will be included in data use agreements with participating practices.

### 11.5 Safety Oversight

Safety oversight will be under the direction of a Data and Safety Monitoring Board (DSMB) composed of individuals with appropriate expertise, including a geriatrician, a health services researcher with informatics expertise, and a statistician. Members of the DSMB will be independent from the study conduct and free of conflict of interest. The DSMB will meet at least annually to assess study progress, conduct, and safety data. At this time, each data element that the DSMB needs to assess will be clearly defined. The DSMB will provide its input to the National Institute on Aging / National Institutes of Health staff.

### 11.6 Clinical Monitoring

Not applicable

### 11.7 Quality Assurance and Quality Control

All sites will follow a common quality management plan. Quality control (QC) procedures will be implemented as follows:

**Intervention Fidelity** —Procedures for ensuring fidelity of intervention delivery and collection of semi-structured interview and survey data are described in the **Manual of Procedures (MOP)** and in **Section 7.2.1, Interventionist Training and Tracking**.

**Metrics.** The DARTNet Institute will perform quality checks and data cleaning using proprietary software and systems, and will format data into OMOP v6 data models with SNOMED and RxNorm codes. Data quality will be enhanced through a series of programmed data quality checks that automatically detect out-of-range or anomalous data.

**Protocol Deviations** – The study team will review protocol deviations on an ongoing basis and will implement corrective actions when the quantity or nature of deviations are deemed to be at a level of concern.

### 11.8 Data Handling and Record Keeping

#### 11.8.1 Data Collection and Management Responsibilities

***Semi-structured interviews***

Data collection activities include collecting qualitative audio-recordings of semi-structured interviews. These interviews will be performed by the Principal Investigator and/or a research associate or other team member trained in qualitative research methods. The interviewer(s) will save digital audio recording files on a secure network server or on UCLA Health BOX on the day of collection.

The **MOP** describes procedures for collecting interview audio recordings. There are no case report forms for this study.

***Surveys***

Surveys will be sent to clinicians using personalized links through UCLA Health Qualtrics or REDCap. Downloaded data will be saved on a secure network server or on UCLA Health BOX and will be de-identified. The **MOP** describes procedures for survey distribution.

***EHR data extractions***

Data collection and sharing of data extractions will be carried out in accordance with HIPAA regulations and will follow the execution of Data Use Agreements between UCLA and each of the participating practices, as well as approvals from the UCLA Institutional Review Board. UCLA will also establish a Data Use Agreement with DARTNet to allow for transfer of limited data from UCLA to DARTNet. The DARTNet institute will establish Business Associate Agreements with sites from which they will perform data extractions. Only data relevant to this study will be extracted and transferred. Adequate provisions will be established to ensure the security of the data and to maintain its confidentiality. All data will be protected by HIPAA-compliant IT systems and will be uploaded on HIPAA-compliant cloud storage systems.

Data coordinating center. The DARTNet Institute will serve as the data coordinating center. DARTNet will receive limited data from the participating organizations or will establish an agreement to extract data from the organization’s EHR system. A list of data elements to be extracted can be found in [Section 13 Appendix](#_13_APPENDIX).

DARTNet Data Environments**.** DARTNet maintains HIPAA compliant data in two different environments. Physical machines are housed in a HIPAA-compliant server room maintained by the central IT department of the University of Colorado, Denver. Access is monitored 24 hours a day, 7 days a week with key card monitoring and video recording. All DARTNet servers are on their own sub-network behind a second firewall maintained by DARTNet, along with a second intrusion detection system also maintained by DARTNet. Electronic access is through the University of Colorado, Denver VPN and access to all servers requires duo-factor authentication. All servers are scanned at least monthly for vulnerabilities. Third party risk assessments and intrusion tests are conducted annually. All servers are regularly patched. They are also encrypted at rest and selected systems overlay database level encryption on the disk level encryption system.

DARTNet also maintains a HIPAA-compliant cloud-based computing center. This center is physically hosted by Amazon Web Server in the Portland, OR area. All systems are encrypted and all access is through individual user accounts using secure portals.

AAFP NRN Data Environments. The American Academy of Family Physicians National Research Network (AAFP NRN) has a secured, HIPAA compliant server on the University of Colorado – Denver system to conduct data management and analyses on data that requires HIPAA compliance. This network is the same network that houses DARTNet Institute’s environment, though on different servers. On this server, a SAS license is provided for data management and analysis. The data used in this project will be stored on this server and within DARTNet Institute’s Egnyte system. Egnyte is also a HIPAA compliant storage system and file transfer system.

The DARTNet Institute will extract or receive data from practices and process it through their Egnyte system. The AAFP NRN will access data from the secured HIPAA compliant server after initial processing by DARTNet. After downloading, the AAFP NRN will clean the data and create limited analytic datasets that will be transferred to UCLA for analysis. Technical safeguards will be in place to protect storage and transmission, including end-to-end encryption and firewall protection.

UCLA Health Data Environments. UCLA will receive and maintain limited datasets from the AAFP NRN. The AAFP NRN will save these files directly into a HIPAA-compliant cloud-based computing system such as BOX storage, where the data will be maintained. Technical safeguards will be in place to protect storage and transmission, including end-to-end encryption and firewall protection. Electronic access will be via a unique user identification and password.

#### 11.8.2 Study Records Retention

De-identified quantitative data on the population cohort of patients will be placed in a data repository and maintained indefinitely.

Audio recordings of semi-structured interviews, de-identified transcripts, and survey data will be maintained indefinitely. Patient contact information will be deleted at the end of the study. Permission is not required prior to the destruction of this information.

### 11.9 Protocol Deviations and Non-Compliance

It is the responsibility of the investigator to use continuous vigilance to identify and report deviations and/or non-compliance to the UCLA Institutional Review Board. All deviations must be addressed in study documents, reported to the National Institute on Aging Program Official and to the UCLA Institutional Review Board. The investigator is responsible for knowing and adhering to the reviewing IRB requirements.

#### 11.9.1 NIH Definition of Protocol Deviation

A protocol deviation is any changed, divergence, or departure from the IRB-approved research protocol.

- Major deviations: Deviations from the IRB approved protocol that have, or may have the potential to, negatively impact the rights, welfare or safety of the subject, or to substantially negatively impact the scientific integrity or validity of the study.
- Minor deviations: Deviations that do not have the potential to negatively impact the rights, safety or welfare of subjects or others, or the scientific integrity or validity of the study.

### 11.10 Publication and Data Sharing Policy

#### 11.10.1 Human Data Sharing Plan

This study will be conducted in accordance with the following publication and data sharing policies and regulations:

National Institutes of Health (NIH) Public Access Policy, which ensures that the public has access to the published results of NIH funded research. It requires scientists to submit final peer-reviewed journal manuscripts that arise from NIH funds to the digital archive PubMed Central upon acceptance for publication.

This study will comply with the NIH Data Sharing Policy and Policy on the Dissemination of NIH-Funded Clinical Trial Information and the Clinical Trials Registration and Results Information Submission rule. As such, this trial will be registered at ClinicalTrials.gov, and results information from this trial will be submitted to ClinicalTrials.gov. In addition, every attempt will be made to publish results in peer-reviewed journals. Data from this study may be requested by other researchers after the completion of the primary endpoint by making a request through the University of California Curation Center (UC3), which maintains the Dryad publishing platform.

#### 11.10.2 Genomic Data Sharing Compliance

Not applicable

### 11.11 Collaborative Agreements

#### 11.11.1 Agreement Type

Not applicable

### 11.12 Conflict of Interest Policy

The independence of this study from any actual or perceived influence is critical. Therefore, any actual conflict of interest of persons who have a role in the design, conduct, analysis, publication, or any aspect of this trial will be disclosed and managed. Furthermore, persons who have a perceived conflict of interest will be required to have such conflicts managed in a way that is appropriate to their participation in the design and conduct of this trial. The study leadership in conjunction with the National Institute on Aging has established policies and procedures for all study group members to disclose all conflicts of interest and will establish a mechanism for the management of all reported dualities of interest.

## 12 ABBREVIATIONS

| AAFP NRN | American Academy of Family Physicians National Research Network |
| --- | --- |
| ACIP | Advisory Committee on Immunization Practices |
| AE | Adverse Event |
| AWV | Annual Wellness Visit |
| CDC | Centers for Disease Control and Prevention |
| CFR | Code of Federal Regulations |
| DSMB | Data Safety Monitoring Board |
| EHR | Electronic health record |
| FDA | Food and Drug Administration |
| GCP | Good Clinical Practice |
| HIPAA | Health Insurance Portability and Accountability Act |
| HHS | Health and Human Services |
| ICC | Intra-class correlation coefficient |
| ICH | International Conference on Harmonisation |
| IPPE | Initial Preventive Physical Examination |
| IRB | Institutional Review Board |
| MOP | Manual of Procedures |
| NCT | National Clinical Trial |
| NIH | National Institutes of Health |
| OHRP | Office for Human Research Protections |
| PI | Principal Investigator |
| PT-AWV | Practice-Tailored Annual Wellness Visit |
| QC | Quality Control |
| SAE | Serious Adverse Event |
| SOA | Schedule of Activities |
| UCLA | University of California, Los Angeles |
| UP | Unanticipated Problem |
| US | United States |
| USPSTF | United States Preventive Services Task Force |

##

| Colon cancer | 51-75 years of age | % of patients 50-75 with appropriate colon cancer screening  1) Fecal occult blood test within past 12 months  2) Flex sig within the past 5 years  3) Colonoscopy within the past 10 years  4) CT colonography within the past 5 years  5) FIT-DNA test within the past 3 years | lab_fobt  lab_ifobt_fit  proc_flexible_sigmoidoscopy  proc_colonoscopy  proc_colon_ca_scrn_adenoma  proc_ct_colonography  lab_stool_dna_cologuard | pmh_colorectal_cancer  pmh_total_colectomy  doc_hospice  dx_palliative  dx_frailty  dx_advanced_illness |
| Prostate specific antigen | Men aged 70 years and older | % men 70 and over who were screened for prostate cancer  PSA based screening test performed during the measurement year | gender_male  lab_psa  lab_psa_free | pmh_cancer_prostate  *PSA test in the year prior to the measurement year with result > 4.0 ng/mL (or indication of abnormal test)*  lab_psa  Lab_elevated_psa  *Prescription for 5-alpha reductase inhibitor*  med_a_reduc_inhibit |
| Ultrasound for abdominal aortic aneurysm | Men aged 66-75 years with history of tobacco use  current or past smoker:  dx_tobacco_use  med_tobacco_cessation  ref_smoking_cessation_clinic  soc_past_smoker  soc_smoker  soc_smoker_heavy  soc_smoker_heavy_former  soc_smoker_light  soc_smoker_light_former  soc_smoker_moderate  soc_smoker_moderate_former  soc_smoker_pack_years soc_smoker_years_total  soc_tobacco_cessation  soc_tobacco_current soc_tobacco_past | % men 65-75 who have ever smoked who received 1-time screening for AAA  Abdominal US or other abdominal imaging performed on or after 65th birthday or during measurement period  OR presence of at least 1 AAA in past | gender_male  proc_aaa_screen  proc_abdominal_ct  proc_abdominal_mri  proc_abdominal_us  dx_aaa | soc_non_smoker  soc_tobacco_non_never  doc_hospice  dx_palliative  *within past 6 months*  proc_chemotherapy  *within past 3 months*  doc_nursing_facility |
| Osteoporosis | Women aged 66-75 years of age | % of women 65-75 years of age who received osteoporosis screening  One or more osteoporosis screening tests on or between the patient's 65th birthday and measurement period | gender_female  proc_bmd | dx_osteoporosis  pmh_osteoporosis  med_osteo_prolia  med_osteo_reclast  med_bisphosphonate  med_osteo_tymlos  doc_hospice  dx_palliative  *Exclude if aged 66 and older with BOTH frailty and advanced illness during measurement period*  dx_frailty  dx_advanced_illness |
| Advance Care Planning | Aged 66 and older | % of patients aged 66 and older with documentation of advance care planning | soc_adv_directive | N/A |
| Hepatitis C | Aged 18-79 years of age | % of patients who received one-time hepatitis C screening | lab_hepatitis_c_ab  lab_hepatitis_c_rna  lab_hepatitis_c_genotype  lab_hepatitis_c_screen | dx_hepatitis_c  dx_hepatitis_c_acute  dx_cirrhosis  dx_hepat_carcinoma  dx_decomp_cirrhosis  dx_esophageal_var  dx_hepatic_encep  dx_ascites  doc_hospice  dx_palliative |
| Depression | 1) Entire cohort    2) Those in cohort 1 with positive finding for depression in the past 12 months  dx_depression  dx_depression_major  doc_phq9_gt9 | 1) % of patients who were screened for depression in the past 12 months  2) For those screening positive for depression, % that received follow-up care within 30 days of a positive screen | doc_depression_score  doc_depression_screen  doc_depression_screen_maternal  doc_phq2_score  doc_phq2_screen  doc_phq9_score  doc_phq9_screen  doc_depression_plan  med_antidepressant  med_antidepressant_monotherapy  ref_mental_hlth_psych  ref_behavioral_health_clinic  visit_behavioral_health  ibh_med_antidepressant | dx_bipolar_disorder  *Depression that starts during past 12 months*  dx_depression  dx_depression_major  dx_mental_beh_dis  doc_hospice  dx_palliative |
| Alcohol use | 1) Entire cohort  2) Those in cohort 1 with positive finding for unhealthy alcohol use  soc_alcohol_use_disorder  dx_alcohol_related_disorders  doc_audit_score | 1) % of patients who were screened for alcohol use one or more times within the past 24 months  2) % of patients in Cohort 1 who  screened positive and received an intervention on or up to 60 days after the date of the first positive screen (61 days total) | doc_audit_screen  doc_audit_score  soc_alcohol_screen  soc_alcohol_use_current  soc_alcohol_use_former  soc_alcohol_use_disorder  soc_alcohol_use_none  med_antialcohol  soc_alcohol_counsel_plan  soc_substance_abuse_counsel  ref_alcohol_rehab  ref_drug_addiction_mgmt  ibh_med_antialcohol | soc_alcohol_use_disorder  dx_alcohol_related_disorders  dx_dementia  doc_hospice  dx_palliative  *Exclusion only for cohort 2*  soc_alcohol_use_none |
| Tobacco use | 1) Entire cohort  2) All patients in cohort 1 identified as tobacco users  3) Entire cohort | 1) Screened for tobacco use at least once within 24 months  2) % of patients in Cohort 1 who were identified as tobacco users who received tobacco cessation counseling  3) % of patients who were screened for tobacco use within 24 months AND if screened positive, received intervention on or up to 60 days after the date of the first positive screen (61 days total) | dx_tobacco_use  soc_non_smoker  soc_past_smoker  soc_smoker  soc_smoker_ecigarette  soc_smoker_heavy  soc_smoker_heavy_former  soc_smoker_light  soc_smoker_light_former soc_smoker_moderate soc_smoker_moderate_former soc_smoker_pack_years  soc_smoker_years_total  soc_tobacco_cessation  soc_tobacco_current  soc_tobacco_non_never  soc_tobacco_past  soc_tobacco_screen  soc_tobacco_unspecified  med_tobacco_cessation  ref_smoking_cessation_clinic  soc_tobacco_cessation | doc_hospice  dx_palliative |

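### In the extraction Appendix, the depression and alcohol rows exclude patients on diagnoses that the screening itself can produce, using codes that also define the follow-up cohorts

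*Protocol*

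**What the plan says.** All of this is in the protocol's Section 13 Appendix, in the table of data extraction elements.

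**Depression row.**
- The first metric is the percentage "of patients who were screened for depression in the past 12 months".
- The second cohort is "Those in cohort 1 with positive finding for depression in the past 12 months", identified by `dx_depression`, `dx_depression_major` or `doc_phq9_gt9`. Its metric is the percentage "that received follow-up care within 30 days of a positive screen".
- The exclusion column includes "Depression that starts during past 12 months", followed by `dx_depression` and `dx_depression_major`. No exclusion in the row is tied to one cohort.

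**Alcohol row.**
- Screening is counted over 24 months.
- The second cohort is "Those in cohort 1 with positive finding for unhealthy alcohol use", identified by `soc_alcohol_use_disorder`, `dx_alcohol_related_disorders` or `doc_audit_score`.
- The first two of those codes are also in the exclusion column, with no date. The note "Exclusion only for cohort 2" stands only before `soc_alcohol_use_none`.
- `soc_alcohol_use_disorder` is in the inclusion/numerator list as well.

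Depression and alcohol screening are Table 2 services (Section 4). They are therefore secondary endpoints (Section 10.4.3) and candidates for the composite score, which is a primary endpoint.

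**The concern.** An exclusion from a screening measure should be settled before the screening that it qualifies. Here it is assessed over the same period and can depend on the result. Only a screened patient can be screen-detected, so removing screen-detected patients takes successes out faster than it takes eligible patients out, and the measured rate falls below the true one. As the intervention prompts more screening, more patients become exposed to this rule.

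The second problem is logical. Two codes in each row both admit a patient to the follow-up cohort and remove that patient from the row. A programmer cannot build these cohorts without deciding which column to ignore, and two programmers could decide differently.

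**Working it through.** The plan states no figure on this point, so there is none to reproduce. The first check compares code lists. The second is an illustration on assumed values, because the protocol gives neither screening rates nor new-diagnosis rates for these services.

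**1. Code overlap in the Appendix**

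| Row | Codes defining cohort 2 | Of these, also exclusions | Not overlapping |
|---|---|---|---|
| Depression | 3 | 2 (`dx_depression`, `dx_depression_major`; onset in past 12 months) | `doc_phq9_gt9` |
| Alcohol | 3 | 2 (`soc_alcohol_use_disorder`, `dx_alcohol_related_disorders`; undated) | `doc_audit_score` |

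One alcohol numerator code, `soc_alcohol_use_disorder`, is also an exclusion. A patient whose only evidence of screening is that code can never be counted as screened.

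**2. Timing**

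For depression, the screening window and the exclusion window are both 12 months. Endpoints are taken monthly (Section 10.4.3, Table 7). A patient screened and diagnosed on the same day is out for 12 months and comes back when that screen has aged out of the numerator window. For alcohol the exclusion has no date, so the patient does not come back.

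**3. Error in the level of the screening rate**

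Let s be the true share screened and d the share of screened patients who acquire the excluding diagnosis. Both are assumptions. If no unscreened patient acquires it, the measured rate is

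s(1 − d) / (1 − s·d).

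At s = 50%:
- d = 2%: 0.490/0.990 = 49.5%, 0.5 point too low
- d = 5%: 0.475/0.975 = 48.7%, 1.3 points too low
- d = 10%: 0.450/0.950 = 47.4%, 2.6 points too low
- d = 15%: 0.425/0.925 = 45.9%, 4.1 points too low

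If a share u of unscreened patients also acquires the code, the measured rate is s(1 − d) / [s(1 − d) + (1 − s)(1 − u)]. At s = 50% and d = 10%, u = 5% gives 0.450/(0.450 + 0.475) = 48.6%, and u = 10% gives 50%, which is no error. The figures in the list are therefore upper bounds.

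**4. Error in a 10-point rise** (first formula applied at both ends)

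| True rise | d = 2% | d = 5% | d = 10% | d = 15% |
|---|---|---|---|---|
| 30% to 40% | 9.94 | 9.84 | 9.66 | 9.47 |
| 40% to 50% | 9.98 | 9.94 | 9.87 | 9.78 |
| 60% to 70% | 10.06 | 10.15 | 10.30 | 10.44 |

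For example, 40% to 50% at d = 10% is 47.37 − 37.50 = 9.87. The largest departure is 10 − 9.47 = 0.53 point, and its sign depends on the baseline rate.

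**5. Composite**

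Section 10.2 assumes that patients are eligible for more than 8 services on average. Spread roughly evenly over 8 services, 0.53 point on one service is 0.53/8 ≈ 0.07 point on the composite.

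**The case against.** The best defence is that Section 11.8.1 presents the Appendix as a list of data elements, and Section 10.3 leaves inclusion and exclusion criteria to HEDIS and CMS specifications. On that view, date logic belongs to those specifications or to a statistical analysis plan that is not shown. This stands for rows that carry only undated code lists. In the osteoporosis row ("dx_osteoporosis pmh_osteoporosis") and the hepatitis C row, a dated rule could sit in the external specification. The aneurysm row counts a finding as fulfilment ("OR presence of at least 1 AAA in past"), which shows that services are handled differently, not that the other rows are wrong.

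The defence does not cover the depression row, which states its own time rule, or the alcohol row, where the same codes sit in opposing columns. A general reference to outside specifications does not say which column prevails.

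Three stronger readings are tempting, and the documents do not support them:
- *The follow-up cohorts exclude everyone who defines them.* One of three codes survives in each row, and depression that began more than 12 months ago is not excluded, so coded patients with earlier onset remain. For the same reason, no specific understatement of the follow-up rate can be derived. Table 2 lists the screening services and not follow-up care, so these metrics are not clearly endpoints.
- *The treatment effect is materially biased.* The illustration shows about half a point at most on a 10-point rise, in either direction.
- *Comparisons between practice types or patient groups are distorted.* The documents give no group-specific diagnosis rates from which to show this. The racial/ethnic disparity objective concerns AWV utilization, and that row of the Appendix has no exclusions.

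**Conclusion.** The point holds for the depression and alcohol rows. As written, the depression rule removes newly screen-detected patients from the screening measure, and both rows use two of three codes to include and exclude the same people. This is an error in a stated rule, not a missing detail.

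The consequence is modest. It is mainly a downward error in the level of two secondary endpoints: up to 0.5 to 4.1 points at 50% screened with 2% to 15% newly diagnosed, shrinking to nothing if unscreened patients are coded at the same rate. The intervention contrast moves by about 0.5 point or less on a 10-point rise, and the composite by less. The point should be corrected, but it does not threaten the trial's main conclusions.

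The sizes rest on assumed screening and diagnosis rates. Which codes fall under each italic note in the exclusion column is inferred from their order in the table; the overlap of codes does not depend on that.

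**What to change.** In the Appendix:

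1. Apply the depression and alcohol-disorder diagnosis exclusions only to diagnoses dated before the screening look-back window opens (12 months for depression, 24 for alcohol, as the Appendix sets them). Use the same rule for screened and unscreened patients. The date should not be anchored to the screening test: patients never tested have no such date, and excluding them on diagnosis while keeping those diagnosed after a test would bias the rate upward.
2. State for every exclusion in these two rows which cohort it applies to. Do not apply the diagnosis exclusions to diagnoses made on or after the positive screen that defines cohort 2.
3. Remove `soc_alcohol_use_disorder` from either the numerator list or the exclusion list.
4. For osteoporosis and hepatitis C, only confirm that a diagnosis produced by the screening test does not remove the patient.

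The cost is wording and query logic. The codes are already in the extraction list, but their dates must be kept. One change of population follows: patients with depression diagnosed before the window, who now stay in, would leave the screening denominator, and the protocol should say so.
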